## Abstract

**Background:**

The Cultural Formulation Interview (CFI) is designed to improve understanding of patients’ mental health care needs. The lack of empirical evidence on the impact and effectiveness of CFI use in clarifying people’s perspectives, experiences, context, and identity, and in preventing cultural misunderstandings between migrant patients and clinicians, inspired this study. The objective is to examine the effect of the CFI on the strength of therapeutic working alliances, and the potential mediating or moderating role of perceived empathy.

**Materials and methods:**

A multicenter randomized controlled trial will be conducted, involving migrant patients, their confidants, and clinicians. The CFI will be administered in the intervention group, but not in the control group. Validated questionnaires will be used to assess therapeutic working alliances and perceived empathy. T-tests and linear regression analyses will be conducted to investigate between-group differences and possible mediating or moderating effects.

**Results:**

This study will indicate whether or not the CFI strengthens the therapeutic working alliance between patients and clinicians, as moderated and/or mediated by perceived empathy.

**Discussion:**

Research on the effect and impact of using the CFI in mental health care for migrant patients is important to clarify whether its use strengthens the therapeutic working alliance with clinicians. This can lead to a reduction in cultural misunderstandings and improve mental health care for migrant patients. The results may also be important for the implementation of the CFI as a standard of care.

**Ethics and dissemination:**

This research protocol was tailored to the needs of patients in collaboration with experts by experience. It was approved by the Ethical Review Board of the Tilburg Law School and registered in the Clinical Trials Register under number NCT05788315. Positive results may stimulate further implementation of the CFI in clinical practice, and contribute to improving the impact of the CFI on the therapeutic working alliances.

## Introduction

Due to cultural differences between patients with a migrant background (hereafter: migrant patients) and clinicians, mental health care faces many challenges. Such differences cause higher thresholds for help-seeking and incongruencies in diagnosis and treatment, which do not meet these patients’ needs (1). Challenges stem from language barriers, diverse idioms of distress, and distinct explanatory models between migrant patients and predominantly non-migrant mental health providers (2). Idioms or expressions of distress provide alternate means of conveying emotional upset and are indicative of personal and cultural contexts. In mental health care, migrant patients experience higher dropout rates, longer care trajectories, lower treatment effectiveness, and more frequent involuntarily admissions to clinical care (3, 4). Despite the positive fact that migrant patients’ access to mental health care appears to have improved, they often do not receive the necessary care (5). This could result from a limited view of these patients experiencing mental health symptoms and inadequate focus on their social context, cultural roots, environment, and cultural identity, which fails to recognize and comprehend the individual behind the patient (6, 7). Despite the consideration of migrant patients’ cultural identities in diagnostic procedures to gain better insights into their symptoms, these patients continue to receive inadequate diagnoses and often feel misunderstood (1, 6, 7).

To address miscommunication in diagnosis and treatment, initiatives have been taken to include cultural identity, idioms of distress, support systems, and clinician-patient relationships in interviews (1, 8). In 2013, the Cultural Formulation Interview (CFI) was included in the fifth edition of the Diagnostic and Statistical Manual of Mental Disorders (DSM-5) (9). This semi-structured interview incorporates the migrant patient’s social and cultural context and addresses beliefs, customs, and identity in the diagnostic and treatment process. The interview aims to increase mutual understanding and rapport between patients and clinicians based on an interest in and a better understanding of the cultural background of these patients to prevent cultural misunderstandings (10). The CFI was found to be a feasible, acceptable, and useful instrument in mental healthcare and it is used increasingly among different populations worldwide (11–13). In general, therapeutic working alliances benefit from the use of the CFI (7, 14). However, CFI use can also negatively affect communication and the therapeutic working alliance between migrant patients and clinicians when questions about culture may upset the patients and jeopardize the quality of the alliance (7, 15, 16). To avoid the latter scenario, it is recommended to train clinicians in the use of the CFI, provide supervision, and focus on compliance and fidelity in administering the interviews (7). It is still unclear whether this strategy creates stronger therapeutic working alliances, which may contribute to reducing high dropout rates, improving treatment outcomes, and enhancing the quality of mental health care (7).

One of the most important factors in mutual understanding between migrant patients and clinicians is empathy. Empathetic clinicians will better understand their migrant patients than non-empathic clinicians (17). Empathy is described as the accurate recognition of the internal frame of reference of a person other than oneself, integrated with the emotional components and implications of imagining oneself as the other person (18). Empathy is part of building relationships between patients and clinicians (19). Empathy may be even more important in culturally sensitive mental health care. Cultural empathy embodies the ability to identify with the feelings, thoughts, and behaviors of people from cultural backgrounds different from one’s own by listening and hearing beyond the spoken word and bridging cultural differences (20).

Evidence of the effectiveness of the CFI in clinical practice is still lacking (6). An exploratory qualitative study among migrant patients found tentative optimistic signs regarding satisfaction, recognition, and clarity of the effect of cultural formulation (21). However, resistance to CFI implementation was also reported from both migrant patient and clinician perspectives. This resistance was based on the experience of some problematic CFI questions (7). The present study aims to clarify whether the CFI leads to stronger therapeutic working alliances and if this association is mediated and/or moderated by higher perceived cultural empathy. The results may contribute to better suggestions for mental health assessments. If the use of the CFI is found to be beneficial to the therapeutic relationship, intake, diagnostic, and therapeutic protocols in clinical mental health care could be adapted and improved. In addition, the timing of administration of a CFI could be optimized and protocolized, including experiential learning in intake, diagnostic, and treatment procedures.

It is hypothesized that this study will show that implementation of the CFI may have a positive, strengthening effect on the therapeutic working alliance between migrant patients and clinicians moderated by (perceived) cultural empathy. Therefore, the central research question of this study is: Does the use of the CFI influence the therapeutic working alliance between migrant patients and clinicians? In addition, it will be examined whether perceived cultural empathy moderates (changes strength and direction) or mediates (explains) the effect of CFI use on the therapeutic working alliance.

## Methods and analyses

### Study design

This study has been designed as an RCT among migrant outpatients newly admitted to mental health care and their clinicians in four mental health care settings in the Netherlands. Experiential expertise and knowledge were crucial in this study design. Five experts by experience were recruited to help plan this research when providing their services at one of the participating locations. They contributed significantly to the study design. Four experts by experience will assist the researchers with recruitment and enrollment, which may lower the participation threshold for migrant patients. Their assistance in answering questions during the data collection period may lead to increased enrollment, adherence, and better outcomes. In addition, the experts will assist with the interpretation of the results based on their experiences and their expectations.

### Study context

There is a lack of scientific evidence regarding the effect of using the CFI on therapeutic working alliances. To the best of our knowledge, this study is the first to use an RCT to investigate this effect, including the exploration of the moderating or mediating effect of cultural empathy. To enhance the quality of this research, and acknowledge the growing importance of experiential expertise in mental health care, experts by experience were democratically involved in the development of this research protocol, the establishment of the research questions, highlighting the research topic from their perspective, and included as coauthors in this paper.

Funding for this study was provided by ZonMw under grant number 6390039231 based on the argument that the aim of this study is highly relevant for improving the quality of mental health care for patients with a migration background. Based on the results of the study, ZonMw advised contacting health insurance companies to support the implementation of the CFI as a standard care practice if this study yields significant results. This study will be conducted in accordance with the tenets of the Declaration of Helsinki (22). The study protocol was approved by the Ethical Review Board of Tilburg University under identification code TLS_RP978 and registered in the Clinical Trials Register under the number NCT05788315.

### Co-creation and user involvement

Experts by experience played an important role in determining the study parameters, based on their personal experiences with mental health symptoms and mental health care, such as stigma and empowerment. They know from experience how important it is to create a supportive environment for patients in need of mental health care and how this can enhance supportive recovery care (23–25). Their cultural background and personal experience with mental health symptoms, treatment, and recovery trajectories distinguish them from clinicians and researchers, highlighting the research topic from their perspective. The experts by experience have particularly emphasized the importance of incorporating empathy into the study design. Based on their practical experience and knowledge, they are able to understand patient’s associated feelings of vulnerability with mental health symptoms. This understanding allows migrant patients to feel safe and authentic during their interactions. In addition, they are able to empathize with migrant patients and recognize coping strategies to address mental health symptoms. Experts by experience also advised to include migrant patients’ confidants such as a partner, family member, close friend, or other support contacts to participate in this study to learn from their experiences with the migrant patient’s mental health. Their input could be beneficial to both the migrant patient and the clinician by clarifying the migrant patient’s circumstances from their perspectives. Therefore, the experts by experience will continue to contribute to the conduct of this study (17).

### Participants

Participants eligible for inclusion in this study are adults aged 18 and over who have a personal or family history of migration, are voluntarily admitted for outpatient mental health care, and are able to communicate their vision, context, and expectations for the treatment and care provided. Migrant patients were included regardless of their administrative status. In addition to the migrant patients, clinicians, and, where applicable, a migrant patient’s confidant will also participate in the study. Inpatients and patients who undergo compulsory treatment are excluded from participation to avoid bias through compromised therapeutic working alliances due to the complex nature of the mental health problems presented in inpatients and involuntary admissions. Participants are excluded when they suffer from acute mental illnesses, such as psychotic episodes, that prevent them from adequate participation.

In Dutch mental health centers, care is provided by multidisciplinary teams of clinicians consisting of psychiatrists, psychologists, psychiatric nurses, social workers, and various types of specialist therapists. Some mental health centers have specialized transcultural teams that were recruited for participation in this study. Participating clinicians must be willing to adhere to the study protocol. The participating Dutch mental health centers are the Center for Transcultural Psychiatry Veldzicht, ProPersona, Parnassia, and GGZ Drenthe. Each center will try to include a representative group of participants in this study. The aim is to have an equal number of participants in the intervention and control groups in each participating center. Data collection will take place between June 2023 and June 2024.

### Procedure

**Figure 1** illustrates the recruitment and inclusion procedure in this study. Before migrant patient enrollment, clinicians at each mental health center will receive an information letter about the study. They will also receive a link to an online informed consent form and some demographic questions. Subsequently, all participating clinicians will be instructed on how to apply the inclusion criteria for ongoing recruitment and will be trained to administer the CFI to increase the level of adherence to the intervention and study protocol. Therefore, clinicians will be invited to participate in a two-hour training session for the CFI at their site. The session includes a review of the core guidelines, a 24-minute video demonstration, interactive behavioral simulations with coaching and feedback from local principal researchers, and a question-and-answer session. All clinicians at participating centers are encouraged to follow the interview structure throughout the study to ensure consistency regardless of the status of the migrant. During the term of the study, the researchers will schedule at least two, or more if necessary or requested, evaluation moments with the clinicians to assess the recruitment of participants, the administration of the CFI based on fidelity checks, and personal experiences with the study protocol. The experts by experience will be contact persons for each of the centers and will participate in the CFI training and instruction at the center to which they were assigned.

**Figure 1 f1:**
[figure not shown]
The Procedure of Cultural Formulation Interview Randomized Controlled Trial.

### Recruitment of migrant patients and confidants

Clinicians will recruit migrant patient participants during their intake sessions. They will provide brief information about the study, and hand out an information letter on behalf of the researchers. The information letter is made available in several languages, including Dutch, English, Spanish, French, Turkish, classic Arabic, and Farsi. Translations have been done and/or reviewed by at least two native speakers of each language. Clinicians will be instructed to ask the potential participants for permission to provide their name, email address, and/or telephone number to the principal investigator in a secure online environment, with permission to be contacted by the principal investigator after one week regarding participation. During this follow-up, any questions about participation will be answered, information clarified, and, if the patient agrees to participate, an appointment will be made to sign the informed consent form and complete some demographic questions. Additionally and when applicable, contact information for a confidant who is willing to participate will be collected, and confidants will be contacted using the same process as the migrant patients. The informant version of the CFI (CFI-I) will be administered by the migrant patient’s clinician in accordance with the patient’s randomization. Clinicians and confidants will also have to sign an informed consent form before participation. Participation is voluntary, does not jeopardize treatment, and participants are free to withdraw their consent to participate at any time without explanation or negative consequences. The researchers or clinicians may decide to withdraw a patient from the study for urgent medical reasons. The procedure of this study is shown in **Figure 1**.

### Randomization

After enrollment, the migrant patients will be randomly assigned to the intervention or the control group by the principal investigator. During the data collection period, the data will not be fully anonymous, because the principal investigator needs to be able to plan appointments for data collection with both the migrant patients and clinicians and to avoid the risk of making mistakes in assigning the collected data to the correct participant ID in the main data file. Patients are single-blinded while their clinicians will be notified of the randomization status to use the CFI or adhere to standard care. Randomization will be set up based on the output of the online tool, Research Randomizer (26). Four groups, representing the four mental health centers and 100 participants per center, are entered into the tool. The resulting four sets of random order numbers, up to 100, are stored and used to randomize participants. Set 1 is used for GGZ Drenthe, 2 for Parnassia, 3 for CTP Veldzicht, and 4 for ProPersona. Odd numbers indicate the intervention group and even numbers indicate the control group. The order of the numbers defines the allocation to the respective participants in the order of inclusion. The same numbers are also used as ID numbers for the participants. The letters D, U, V, and P are added to the ID numbers to indicate the mental health center; D for GGZ Drenthe, U for Parnassia, V for CTP Veldzicht, and P for ProPersona. In addition, the letters MP for the main participant, C for clinician, and Co for confidants are added to the numbers to identify the role of the participants in the study. In this way, the number and treatment center letter link the participant to their clinician and confidant, making them anonymous but identifiable in their association. Before data analyses, the data file will be fully anonymized and the coding system changed by non-analyzing researchers to blind the researchers performing the analyses from knowing which participant was allocated to the intervention or the control group, and in which mental healthcare center they participated.

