### Data collection

For the duration of the study, migrant patients will be assigned to a personal clinician as they will be required to complete questionnaires about each other. Before the start of treatment, clinicians will be informed of the randomization group to which the migrant patient has been assigned. Participating confidants will have one consultation with the personal clinician of the patient that they represent, according to the patient’s randomization status.

The principal investigator will receive notification regarding the date of the initial treatment session to schedule an appointment for the migrant patient to take the first-stage survey on perceived empathy, either face-to-face or online. The respective questionnaires must be completed within one week of the first session, and interpreters will be employed as necessary. The patient proceeds with subsequent treatment following the treatment plan. The procedure for participating confidants will be identical, and their involvement will cease upon finishing the perceived empathy questionnaire (see **Figure 1**).

In the intervention group, treatment sessions will proceed using CFI questions. The control group will receive standard care in which CFI questions are avoided. After each initial treatment session, clinicians will complete a brief online questionnaire to evaluate their fidelity to the CFI. Fidelity is expected for migrant patients who were randomized in the intervention group, and infidelity to the CFI is expected in the control group. In addition, the clinicians will be asked to respond to empathy-related questions.

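### The principal investigator both contacts patients about taking part and allocates them from stored lists, and no separation between enrolment and the lists is stated

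*Protocol article*

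**What the plan says.** All references are to the Protocol article.

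- **First approach** (Recruitment of migrant patients and confidants): "Clinicians will recruit migrant patient participants during their intake sessions". They pass on contact details, "with permission to be contacted by the principal investigator after one week regarding participation".
- **Consent** (same section): in that follow-up, "if the patient agrees to participate, an appointment will be made to sign the informed consent form and complete some demographic questions". The sentence does not say who answers questions or takes the signature.
- **Help with enrolment** (Study design): "Four experts by experience will assist the researchers with recruitment and enrollment".
- **Allocation** (Randomization): "After enrollment, the migrant patients will be randomly assigned to the intervention or the control group by the principal investigator". The sets come from an online randomizing tool. "The resulting four sets of random order numbers, up to 100, are stored and used to randomize participants". Odd means intervention and even means control. "The order of the numbers defines the allocation to the respective participants in the order of inclusion".
- **Blinding**: the section on Randomization has non-analyzing researchers recode the file before analysis. The section on Data collection and management blinds the principal investigator at that same stage. Clinicians are told each patient's arm; patients are not.
- **Choice of clinician** (Data collection): "migrant patients will be assigned to a personal clinician as they will be required to complete questionnaires about each other". Whether this happens before or after allocation is not stated.

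**The concern.** Allocation is concealed when whoever influences a patient's entry cannot know which arm comes next. Here one role makes the contact about participation and also applies a stored list whose code is simply odd or even. If that person can see the next number, the arm may affect how warmly a patient is encouraged or when the appointment is booked.

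Two features of this trial raise the stakes. The outcome is a subjective rating of a patient–clinician relationship. And Table 1 lists only consent and demographic questions at enrolment, with no baseline alliance or empathy score, so selection on likely alliance could be neither detected directly nor adjusted for. The results are also meant to support a case to health insurers, which makes avoidable doubt about the randomization costly.

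**Working it through.** The plan states no figure on this point, so the main check sets the steps in time order.

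| Step | Who acts, as stated | Protection of the list, as stated |
|---|---|---|
| 1. Approach at intake | Clinician | None stated; no text gives clinicians the list |
| 2. Contact after one week | Principal investigator | None stated |
| 3. Consent appointment and demographics | Arranged in step 2; signature taker not named | None stated |
| 4. Allocation from the stored set, next number in order | Principal investigator | None stated |
| 5. Clinician told the arm, before treatment starts | Sender not named | Not applicable |
| 6. Recoding; principal investigator blinded | Non-analyzing researchers recode | Present, but only before analysis |

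Concealment matters in steps 1 to 4. The only safeguards stated are in step 6. That allocation follows enrolment (step 4) says when a number is applied, not when it can first be seen.

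**How predictable is the next arm?**

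- *With the list in view:* the parity of the next number gives the arm with certainty.
- *Without the list:* the best guess is the arm used less often so far in that centre. Simulating the stated scheme (random order of 1 to 100, odd/even code, 20,000 runs) gives 51.9% correct over the first 41 patients (164/4 = 41, assuming equal recruitment across centres) and 55.8% over all 100.
- *Closed-form check for all 100:* [50 + (2^100/C(100,50) − 1)/2]/100, with 2^100/C(100,50) ≈ 12.56, gives (50 + 5.78)/100 ≈ 55.8%. This agrees with the simulation.

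The sequence is hardly guessable, so the question is access to it.

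**Would blocking help?** The same guess with known blocks of 4 succeeds in (2 + (16/6 − 1)/2)/4 = 70.8% of cases, and with blocks of 6 in (3 + (64/20 − 1)/2)/6 = 68.3%. Recruiting clinicians learn the arms of their own patients, so blocking would make the sequence easier to guess.

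**Illustration only.** Assume a net bias of b standard deviations in the mean WAI, no true effect, 82 patients per arm (164/2), and a two-sided t-test at 5%. The noncentrality is b × √(82/2) = 6.403b.

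| Assumed b | Noncentrality | Probability of rejection |
|---|---|---|
| 0.10 | 0.640 | 9.8% |
| 0.15 | 0.960 | 15.9% |
| 0.20 | 1.281 | 24.7% |

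Nothing in the documents supports any particular b.

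**The case against.** The strongest reply is that this is a condensed article. It does not say who generated or holds the sets, or whether upcoming numbers are visible, so the full protocol may contain a safeguard. That stands as a limit on the conclusion: one may not say that the next arm *is* known before consent. It does not remove the point, because the article itself gives contact and allocation to one role, and that is a stated procedure rather than missing detail.

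Several stronger readings are tempting and are not supported:

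- *The principal investigator consents patients and fixes their order.* The text names this role only for the contact. Clinicians' referrals come first, and experts by experience assist, so the principal investigator can influence the order but is not shown to set it.
- *Clinicians experienced with the CFI are steered to CFI patients.* This rests only on silence about when, and by whom, the personal clinician is chosen. The plan does intend to explore clinicians' work experience and prior CFI experience, although that would not restore concealment.
- *The type I error is 10% to 25%.* Those figures follow from assumed biases. The WAI is first completed after the fifth session and rates a relationship that has not formed at enrolment, so selecting patients by expected score would be hard.

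**Conclusion.** The point holds in a limited form. One role both arranges participation and allocates from stored centre lists with an open code, no separation between the two is stated, and blinding starts too late to protect enrolment. Confidence in that overlap is high, because it is in the text. That the person enrolling actually sees the next arm is an inference, which an undescribed safeguard could overturn.

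Selection bias is possible, not shown, and its size cannot be estimated from the documents; the rejection probabilities above describe assumed biases and not this trial. The matter should still be settled before enrolment, since no analysis can restore concealment afterwards and there is no baseline alliance score with which to look for damage.

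**What to change.** Remove the principal investigator's access to the four lists during enrolment. Have a non-analyzing researcher (a role already in the plan) hold them, or load them into the Qualtrics system already used for data collection. Release one assignment at a time, only after signed consent and demographics are recorded, and preferably after the personal clinician has been named. Keep the sequence as it is; blocking is not needed for concealment.

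If a safeguard already exists, stating who holds the lists and when each number is revealed is enough. If patients have already been enrolled under the procedure as described, record who had access to the lists and from when, and report it.

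The cost is a short set-up, a protocol change and a small delay per assignment. It requires no additional patients and uses a role or system already in the plan. The principal investigator can still learn each arm after release, as scheduling requires.
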